**Fig. 2 Fig2:**
[figure not shown]
The electronic and paper portable health files

Several levels of password protection and doctor authentication are required. The e-PHF runs from the USB flash drive which also includes antivirus software. The USB flash drive also carries the software allowing it to be installed on computers of any new health-care provider once the patient has provided permission. Written as well as online information regarding the project and installation is provided, as well as a free 1800 telephone support number. Information regarding the study is incorporated on a tag that is attached to the USB flash drive and the 1800 telephone number is engraved onto the USB flash drive. Self-installation is encourage to evaluate the projects sustainability, and a record will be kept of how many health-care providers self-installed the software from the patient’s USB flash drive versus having the project support team install the software.

Once the patient has securely entered their password and the e-PHF application launches, the health-care provider has the opportunity to become an authenticated user. This requires the health-care provider to contact the study personnel on an 1800 support number. Once the health-care provider generates their own password, and after the study personnel authenticates the health-care provider’s identity, the health-care provider is given an authentication key. This authentication process only can proceed if the USB flash drive is connected to the host computer. The authentication key creates synchronized a record of the entire e-PHF on the host computer to allow the provider to read (but not write to) the e-PHF record after the patient has left the consultation, without requiring connection of the patient’s USB flash drive. However, security is still enforced, as the health-care provider must enter their password to launch and read the patient’s read-only record.

If the USB flash drive is lost, the data is encrypted and cannot be accessed without the patient’s password. A new USB flash drive can be repopulated with the entire e-PHF, once password protocols are met, and the patient takes the new USB flash drive to the last authenticated user. There are a number of other features of the e-PHF, designed to improve accuracy and acceptability, which are not provided in this protocol.

#### Paper portable health file

The p-PHF was designed to implement the objectives of the study. It is a color-coded, 280-page, A6 ring-bound book in 39 sections that contains general information, medical and other health-care related information. It contains a health-care provider section in part A, and a patient section in part B (Figs. 2 and 3). As it is paper the book is not secured. If the book is lost, then only the pages that were scanned at the six-monthly intervals by the study personnel can be repopulated in another p-PHF, unless a health-care provider or the patient has copied the pages in the intervening period.

**Fig. 3 Fig3:**
[figure not shown]
Excerpt from contents of the paper portable health file

### Trial arms

#### Arm one: electronic portable health file

Arm one is the e-PHF added to usual care. The e-PHF will be kept by the subject (or caregiver) and taken to health provider visits. At each visit the health-care provider has the opportunity to read the contents of the e-PHF. The health-care provider then has the opportunity to write to the e-PHF. The information that is recorded is information that is deemed relevant by the health-care provider. It can be a record of the entire visit or a summary of the visit. The current visit information can subsequently be printed, exported or copied and pasted into another file. Information that the health-care provider believes the patient may not want disclosed to other health-care providers is discussed with the patient, and a decision is made whether it should be recorded in the e-PHF or not. The medical information that can be recorded includes recent and past medical problems and conditions, examination findings, investigations requested and their results, current medications, medication changes, any adverse events, condition management plans and clinical audits of the processes of care derived from best practice guidelines. Patients can also enter this information in their patient section. Patients have access to read all sections of the e-PHF, but can only write to the patient section.

#### Arm two: paper portable health file

Arm two is the p-PHF added to usual care. The p-PHF intervention in content is similar to the electronic counterpart, but is paper-based within an A6 spiral bound book.

#### Arm three: usual care

Arm three has no PHF and is usual care only.

#### Additional procedures

All subjects randomized to either the e-PHF or p-PHF will receive a PHF pre-populated with a summary of their baseline medical history, including past and current medical conditions, current medications and alerts. This information is obtained after an interview with one of the study’s medical investigators, who is a medical doctor and who has access to the GP, specialist and hospital medical records for verification. Once the PHF has been prepared with the patient’s medical information, the patient is asked to verify that the information is correct. Patients randomized to usual care also undergo the same processes, but the information is not used to populate a PHF and is kept for analysis purposes.

All patients also complete a baseline questionnaire that includes items on demographic information, social and lifestyle information, experience with computers, quality-of-life information, health-care utilization, perceptions about personal health files, health-care communication, health-care satisfaction and health literacy.

### Outcomes

#### Primary outcome

The primary outcome is a combined endpoint of the total number of important clinical events, defined as: all overnight hospitalizations, all serious out-of-hospital events and death. Validation of hospitalizations or out-of-hospital events occurs by subject interview, and health-care provider and hospital records as close to real time as is possible. In addition, record linkage with Medicare Australia, Department of Veterans Affairs, Australian Institute of Health and Welfare and NSW Health during the study is another source of valid information on hospitalizations, health service utilization (including a record of all medical encounters) and deaths. Furthermore, an Independent Adjudication Committee (IAC) determines which out-of-hospital events are serious, and are therefore included in the primary combined outcome.

#### Secondary outcome

Secondary outcomes include patient interview and questionnaire self-report data on quality of life (SF-36 and EQ-5D), and whether PHFs are acceptable in terms of user-friendliness, convenience and usefulness to patients and their health-care providers. Additional outcomes include adherence to management plans, duplicate investigations and adverse drug reactions. Subjects will be asked to complete questionnaires at baseline and at regular intervals over the course of the trial (Table 1). The questionnaires include items on health literacy (the short Test of Functional Health Literacy Assessment (TOFHLA) [40, 41] and the Single-Item Literacy Screener (SILS) [42]), experience with information technology, acceptability of and satisfaction with the e-PHF or p-PHF, measures of functional status (SF-36) and utility (EQ-5D), health service utilization, all health-related events, satisfaction with medical care, perception of continuity of care, and adverse events. Additional information will be recorded from the p-PHF and e-PHF to evaluate its real-time use.

**Table 1 Tab1:** Schedule of assessments

Time point (months)	T_0_	3	6	9	12	15	18	21	24	27	30	33	36	39	42	45	48	60	72,84
**PATIENTS**																			
Demographic information	X	X		X		X		X		X		X		X		X	X	X	X
Information technology literacy	X																X	X	X
Health literacy	X																X	X	X
Health and Lifestyle	X																X	X	X
Satisfaction with Health Care	X																X	X	X
Quality of life/SF-36	X	X		X		X		X		X		X		X		X	X	X	X
Health Status/Utility/EQ-5D	X	X		X		X		X		X		X		X		X	X	X	X
Health care utilization	X	X		X		X		X		X		X		X		X	X	X	X
Satisfaction with Health Professional Communication	X																X	X	X
Acceptability of PHF^a^	X																X		
Patient Compliance with PHF^a^		X		X		X		X		X		X		X		X	X		
Health professionals compliance with PHF^a^		X		X		X		X		X		X		X		X	X		
Hospitalizations and Deaths^b^		X		X		X		X		X		X		X		X	X	X	X
Serious out-of-hospital events^b^		X		X		X		X		X		X		X		X	X	X	X
Medications use		X		X		X		X		X		X		X		X	X	X	X
Duplicate Investigations		X		X		X		X		X		X		X		X	X	X	X
Adverse events		X		X		X		X		X		X		X		X	X		
Retrieval of PHF^c^		X		X		X		X		X		X		X		X	X		
Exit interviews																	X		
**HEALTH PROFESSIONALS**																			
Demographic information	X																		
Acceptability of PHF	X																		
Satisfaction with Health Professional Communication	X																		
IT experience	X																		
Compliance with PHF by patient																	X		
Compliance with PHF by health professionals																	X		
Adverse events																	X		
**HEALTH PROFESSIONALS’ MEDICAL RECORDS**																			
Comparison of PHF with health professional medical records^d^																	X		
**RECORD LINKAGE – DATABASE** ^**c**^																			
Deaths																	X		X
Overnight Hospitalizations																	X		X
Day Only Hospitalizations																	X		X
Emergency Department Visits																	X		X
Health care utilization- health professional visits																	X		X
Health care utilization-prescription medications																	X		X

^a^Health Professional compliance will be done only for his/her patients enrolled in the trial. Subject acceptability, satisfaction and compliance will be done on all PHF subjects. Subject compliance will be undertaken by questionnaire and when the interventions are recalled for data extraction. Control no-PHF subjects will also be contacted and given the opportunity to discuss trial-related activities to reduce bias

^b^These assessments will be elicited from the GP and other providers, from subjects or their primary health care givers in real time during the trial. It will be validated by medical record data where possible, then adjudicated by the blinded adjudication committee

^c^Record linkage with NSW State and Commonwealth databases when the last subject has exited the randomized component of the trial and again 3 years after the last subject has exited the trial

^d^GP compliance evaluates data from the medical record with data recorded on the electronic PHF or in the paper PHF

Health-care providers will also provide information regarding their experience with information technology, acceptability of and satisfaction with the e-PHF or p-PHF, uptake of management plans, medication errors, duplicative investigations, health service utilization and adverse events by interview and questionnaire at baseline and at 48 months.

The PHF will be retrieved from the subject at three months and then every six months, and as per the assessment schedule for collection of process measures and clinical outcomes. The p-PHF pages are scanned and the e-PHF data is copied. In the event of loss of the p-PHF, a replacement notebook will be provided will be populated using the patient’s stored information. In the event of a lost USB flash drive, a copy of the latest file can be retrieved from the computer of the last authenticated health provider visited with their e-PHF. If a PHF has been lost this event is documented as an adverse event, but not a serious adverse event.

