### Safety, adverse events and risk assessment

An adverse event is defined in the International Conference on Harmonisation (ICH) Guideline for Good Clinical Practice as ‘any untoward medical occurrence in a patient or clinical investigation subject administered a pharmaceutical product and that does not necessarily have a causal relationship with this treatment’. In this trial, any known breach of PHF security, accuracy and confidentiality, whether intentional or unintentional will be considered an adverse event. A serious adverse event will be considered to be where these breaches lead to physical or emotional harm, as perceived by the participant. All adverse events are adjudicated by the committee. Disclaimers are included in the p-PHF and e-PHF regarding the medical information, and users are cautioned that there is the possibility of error or inaccuracy. The disclaimer also states that the user’s professional and clinical expertise and judgment are required at all times when using the information contained in the PHFs. Adverse events data, including seriousness of the adverse event, is collected with every questionnaire and during retrievals.

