#### Blinding

Once the subject is enrolled in the trial they will be allocated a unique subject identifier, which is a six-digit number without any other identifier (subject ID). Any further documentation associated with the subject will only be identified by this number. Only persons directly related with this trial will have access to the database or stored records. The nature of the intervention does not permit blinding of either trial participants or health-care providers. Therefore, there will be potential for bias in trial conduct and potential for ascertainment bias in the determination of important clinical outcomes and quality of life. To reduce clinical outcome ascertainment bias, a blinded IAC will be used to make the determination which out-of-hospital events are serious. The other primary outcomes, mortality and all overnight hospitalizations, are objective outcomes and are not subject to ascertainment bias. Data on all hospitalizations, same-day hospitalizations, 28-day readmissions and deaths are administrative outcomes, coded and collected by the clinical information systems of public and private hospitals within the state of NSW. Questionnaires that collect information on secondary outcomes are mailed to all trial subjects without any assignment identifiers. All statistical analyses unrelated to acceptability of PHF and compliance of use are masked to intervention allocation via a separate data set.

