**Fig. 4 Fig4:**
[figure not shown]
Pragmatic-explanatory continuum indicator summary of the COMMUNICATE trial

There is formal follow-up of participants to determine serious out-of-hospital events and obtain quality of life and other data, but the primary endpoint is a composite endpoint of hospitalizations (excluding day only), deaths and serious out-of-hospital events, and the former two are obtained from administrative registries. The study has been designed so that the primary outcome is clinically important to patients, caregivers, health-care providers and other health care-related personnel. Participant compliance to the prescribed intervention and practitioner adherence to the protocol are both unobtrusive, although they are measureable at the end of the trial. The primary analysis includes all patients regardless of compliance and practitioner adherence, so that a determination of whether the intervention works under usual conditions is determined. Unlike many other health-care system pragmatic trials, which are cluster randomized, we made a decision to randomize individual patients to the intervention, which provides a greater causal relationship and is more in keeping with an explanatory trial in our setting.

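### The retrieved PHF is named as a source of clinical outcomes but exists only in the PHF arms; the protocol should bar it from originating primary events and say which source governs deaths and admissions

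*Protocol article*

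**What the plan says.** All places are in the protocol article.

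- **Retrieval paragraph after Table 1 (Secondary outcome).** The PHF is collected from the patient on a fixed timetable, "as per the assessment schedule for collection of process measures and clinical outcomes"; paper pages are scanned and electronic data copied. Table 1 puts retrieval at months 3, 9, 15, 21, 27, 33, 39, 45 and 48. These nine time points also carry the rows for hospitalizations and deaths and for serious out-of-hospital events.
- **Safety section.** Adverse event information "is collected with every questionnaire and during retrievals".
- **Arm three.** "Arm three has no PHF and is usual care only".
- **Primary outcome.** "Validation of hospitalizations or out-of-hospital events occurs by subject interview, and health-care provider and hospital records". Record linkage is added as a further source for hospitalizations, service use and deaths.
- **Table 1, footnote b (hospitalizations, deaths and serious out-of-hospital events).** "These assessments will be elicited from the GP and other providers, from subjects or their primary health care givers", followed by validation against medical records where possible and blinded adjudication.
- **Secondary outcome.** The purpose given for PHF data is narrower: "Additional information will be recorded from the p-PHF and e-PHF to evaluate its real-time use".
- **Blinding.** The section accepts a risk of ascertainment bias and answers it with blinded adjudication of out-of-hospital events. It then says that the other two components, "mortality and all overnight hospitalizations, are objective outcomes and are not subject to ascertainment bias".
- **Discussion (text after Fig. 4).** Of hospitalizations and deaths it says "the former two are obtained from administrative registries".

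**The concern.** A PHF can hold recent problems, findings, medication changes and adverse events (Arm one). Someone reading nine scanned or copied files per patient will meet clinical events that neither the patient nor a provider reported. In usual care there is nothing to read. If such an entry can be put forward as a serious out-of-hospital event, the chance that a given event is counted depends on the arm.

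The safeguards do not reach this point. The adjudication committee, as described under Ethics and governance, judges reported events. Blinding therefore makes classification even, but not case finding. Balanced questionnaires and telephone calls even out contact, but they do not give usual care a record to extract.

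Extra detection in the PHF arms raises their event count. It could hide part of a real benefit or resemble harm. The Discussion already allows that hospitalizations may truly rise in the near term under a PHF, so an artefact in the same direction would be hard to tell apart in the composite. The primary model uses recurrent events, so each additional event adds to the count.

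**Working it through.** **Step 1. Sources side by side.**

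| Place | Source or purpose | PHF named? | Present in usual care? |
|---|---|---|---|
| Primary outcome | Interview, provider and hospital records, linkage | No | Yes |
| Table 1, footnote b | GP, other providers, patients, caregivers | No | Yes |
| Secondary outcome | PHF data for real-time use | Yes, usage only | No |
| Retrieval paragraph | PHF for process measures and clinical outcomes | Yes | No |
| Safety section | Adverse events at questionnaires and retrievals | Yes | Questionnaires only |
| Table 1, record linkage rows | Deaths, overnight and day-only hospitalizations, emergency visits, professional visits, prescriptions | No | Yes |

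The retrieval paragraph goes beyond the other source lists. The linkage rows cover deaths and overnight hospitalizations but not serious out-of-hospital events; emergency visits are the nearest row. The exposed component is therefore serious out-of-hospital events.

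**Step 2. The plan's own figures.** Control proportion 0.70, relative reduction 25%, power 0.80, level 0.025 (Sample size and power calculations).
- PHF-arm proportion: 0.70 × (1 − 0.25) = 0.525.
- A two-sided, continuity-corrected comparison of proportions gives 158 per arm, as stated. Exact Fisher power at 158 per arm is 0.803.
- Dropout: 158 / (1 − 0.40) = 263.3, so 264 per arm, and 3 × 264 = 792.

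The stated figures reproduce. They serve only as a baseline here.

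**Step 3. Possible shift in the rate ratio.** The documents give neither the share of out-of-hospital events nor any rate of PHF-only detection, so both are assumed. Let s be the share of out-of-hospital events among all events (2-10%) and e the relative excess found in a PHF arm (10-50%).

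Observed ratio = true ratio × (1 + s × e)

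| s | e | 1 + s × e | True 0.75 reads as | True 1.00 reads as |
|---|---|---|---|---|
| 0.02 | 0.10 | 1.002 | 0.7515 | 1.002 |
| 0.05 | 0.25 | 1.0125 | 0.7594 | 1.0125 |
| 0.10 | 0.50 | 1.05 | 0.7875 | 1.05 |

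**Step 4. Sensitivity of the planned test.** Suppose over-detection raises the counted proportion in a PHF arm by a relative k, so that it becomes 0.525 × (1 + k).

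| k | Proportion | Apparent reduction | Fisher power, 158 per arm |
|---|---|---|---|
| 0 | 0.525 | 25% | 0.803 |
| 1% | 0.530 | 24.3% | 0.775 |
| 2% | 0.536 | 23.5% | 0.746 |
| 5% | 0.551 | 21.3% | 0.648 |

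Here k counts patients with at least one event, while s × e counts events. The two are not interchangeable, and the primary analysis is an Andersen-Gill model, so this table is only indicative.

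**Step 5. Deaths and overnight hospitalizations.** The Discussion takes these from registries. The Primary outcome section places linkage beside interviews and provider records. Footnote b has them elicited from providers, patients and caregivers, and under Blinding the patients and providers know the allocation. These statements can coexist, but none says which source governs when they disagree. The Blinding statement needs that rule: it holds if administrative or linked data decide, and is unsupported if an admission found by interview alone can count.

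**The case against.** The strongest reply is that no sentence takes primary events from the PHF. The two places that define primary ascertainment omit it, the retrieval paragraph sits under secondary outcomes, and Table 1 lists retrieval on a row of its own. The phrase can also be read as describing the assessment schedule, and the clinical outcomes it mentions are undefined and may be non-primary. This stands. A reader might infer that primary events are in fact extracted from the PHF; the documents do not show that. They show a source available in two arms whose permitted use is left open.

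A reader might also infer that the Blinding statement is refuted. It is not. That sentence covers only deaths and overnight hospitalizations, which have administrative sources common to all arms and are to be ascertained even after withdrawal. For out-of-hospital events the same section concedes the risk. Nor does the Discussion say that registries are the sole source, so the passages on source are incomplete rather than flatly contradictory.

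Usual care is also not left to memory. Hospital records, linkage, balanced questionnaires and telephone inquiries apply to every arm. Some adverse events collected at retrieval, such as breaches of PHF security, could not occur without a PHF and are not primary events.

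Finally, the protocol expects few serious out-of-hospital events and expects hospitalizations to dominate, which argues for the low end of the range. The bias runs against the PHF, so it would not manufacture a claim of benefit. What remains after these points is unequal case finding for one component and the absence of a governing source for the other two.

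**Conclusion.** The point holds in a limited form. If PHF content can originate a serious out-of-hospital event, case finding differs by arm, and neither blinded adjudication nor linkage corrects it. Under the assumed shares and over-detection, a true rate ratio of 0.75 reads as about 0.75-0.79 and a true 1.00 as about 1.00-1.05. That is small beside the 25% target, and smaller still if these events are as rare as expected. No demonstrated failure of the primary endpoint follows. For deaths and overnight hospitalizations, PHF retrieval alone does not undermine the claim of freedom from ascertainment bias; the claim is conditional on a rule that the protocol does not state. The point is worth settling because it decides which events count.

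**What to change.** 1. Amend the retrieval paragraph so that PHF extracts, including e-PHF copies held on providers' computers, serve process and usage measures only and cannot originate a primary event.
2. Send out-of-hospital events to adjudication only when found through channels common to all three arms: questionnaires, telephone inquiries, provider records other than PHF copies, and linked emergency visits.
3. State that linked administrative data govern deaths and overnight hospitalizations in the primary analysis, for all randomised patients.
4. Make the Blinding statement conditional on item 3.

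The cost is wording, since every channel named is already planned. Events recorded only in a PHF or outside the linked databases will not be counted. One leak remains: the Arm one section lets e-PHF visit entries be exported or pasted into another file, so provider records cannot be made wholly independent of the PHF.
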